# EXTUBATE: A randomised controlled trial of nasal biphasic positive airway pressure vs. nasal continuous positive airway pressure following extubation in infants less than 30 weeks' gestation: study protocol for a randomised controlled trial

**DOI:** 10.1186/1745-6215-12-257

**Published:** 2011-12-09

**Keywords:** Preterm birth Infant, Newborn, Humans, Clinical trials, Randomized, Neonatal Intensive Care, Biphasic Continuous Positive Airway Pressure, Continuous Positive Airway Pressure

## Abstract

**Background:**

Respiratory distress syndrome remains a significant problem among premature infants. Mechanical ventilation through an endotracheal tube remains the mainstay of respiratory support but may be associated with lung injury and the development of chronic lung disease of prematurity. Efforts are needed to reduce the duration of mechanical ventilation in favour of less invasive forms of respiratory support and to improve rates of successful extubation.

Non-invasive respiratory support has been demonstrated to be less injurious to the premature lung. Standard practice is to use nasal continuous positive airway pressure (n-CPAP) following extubation to support the baby's breathing. Many clinicians also use nasal biphasic positive airway pressure (n-BiPAP) in efforts to improve rates of successful extubation. However, there is currently no evidence that this confers any advantage over conventional nasal continuous positive airway pressure.

**Methods:**

We propose an unblinded multi-centre randomised trial comparing n-CPAP with n-BiPAP in babies born before 30 weeks' gestation and less than two weeks old. Babies with congenital abnormalities and severe intra-ventricular haemorrhage will be excluded. 540 babies admitted to neonatal centres in England will be randomised at the time of first extubation attempt. The primary aim of this study is to compare the rate of extubation failure within 48 hours following the first attempt at extubation. The secondary aims are to compare the effect of n-BiPAP and n-CPAP on the following outcomes:

1. Maintenance of successful extubation for 7 days post extubation

2. Oxygen requirement at 28 days of age and at 36 weeks' corrected gestational age

3. Total days on ventilator, n-CPAP/n-BiPAP

4. Number of ventilator days following first extubation attempt

5. pH and partial pressure of carbon dioxide in the first post extubation blood gas

6. Duration of hospital stay

7. Rate of abdominal distension requiring cessation of feeds

8. Rate of apnoea and bradycardia

9. The age at transfer back to referral centre in days

The trial will determine whether n-BiPAP is safe and superior to n-CPAP in preventing extubation failure in babies born before 30 weeks' gestation and less than two weeks old.

**Trial registration number:**

ISRCTN: ISRCTN18921778

## Background

Our working hypothesis is that preterm infants born before 30 weeks' gestation and less than two weeks old when extubated on to nasal biphasic positive airway pressure (n-BiPAP) will have a lower risk of extubation failure than infants extubated on to single level, nasal continuous positive airway pressure (n-CPAP).

Respiratory distress syndrome due to surfactant deficiency is almost invariable in infants born at less than 28 weeks' gestation and remains a significant problem in infants born up to 34 weeks' gestation. Mechanical ventilation is the mainstay of treatment in this condition and may be required for prolonged periods of time extending to several weeks. Mechanical ventilation through an endotracheal tube is associated with ventilator associated lung injury which may be a significant factor in the development of chronic lung disease of prematurity (Bronchopulmonary dysplasia) - a condition associated with significant morbidity and mortality among preterm infants. Efforts have been made to reduce dependence on mechanical ventilation using less invasive forms of respiratory support such as nasal continuous positive airway pressure (n-CPAP). In this study we aim to determine if the use of nasal biphasic positive airway pressure (n-BiPAP) is more effective than single level variable flow n-CPAP in preventing extubation failure in babies born before 30 weeks' gestation and less than 2 weeks old.

n-CPAP has previously been shown to reduce the risk of extubation failure among preterm infants following extubation from mechanical ventilation. However, in around 25% of infants attempts at extubation fail [1]. Non-invasive respiratory support has been demonstrated to be less injurious to the preterm lung [2]. Efforts directed to minimise the exposure to or duration of mechanical ventilation in preterm infants have demonstrated the feasibility of early n-CPAP support among extremely preterm infants [3]. In this study, we hypothesise that there can be a further 10% reduction in extubation failures using n-BiPAP compared with n-CPAP.

Nasal Intermittent Positive Pressure Ventilation (NIPPV) has been used as respiratory support post extubation and there is evidence supporting the superiority of NIPPV over conventional n-CPAP in avoiding re-intubation in preterm infants [4]. Infants with birth weight less than 2000 g and mild surfactant deficient lung disease demonstrated reduced work of breathing with synchronised NIPPV compared with conventional n-CPAP [5]. Both of these studies involved the use of the Infant Star ventilator providing continuous flow CPAP with a Star Synch abdominal capsule to deliver synchronised NIPPV. The provision of synchronised NIPPV requires a ventilator capable of delivering this mode of support. The Infant Flow Advance offers a less complex/invasive method for the delivery of n-CPAP/n-BiPAP. n-CPAP with the Infant Flow Driver (a variable flow device) has also been shown to be more effective than CPAP delivered using a continuous flow device in improving oxygenation and reducing work of breathing (see below).

The Infant Flow Advance delivers positive pressure at the nose at two set pressure levels or n-BiPAP. The upper pressure setting is set 3 to 5 cm of water above the base pressure and is delivered for a set "inspiratory" time and a set "rate". With n-BiPAP, there is no synchronisation with the infant's respiratory effort; the infant continues to breathe spontaneously throughout the periods of baseline and upper pressure delivery. There have been two published trials to date which describes the use of n-BiPAP in preterm infants [6,7]. Migliori et al performed an unblinded crossover study comparing four alternating phases of n-CPAP and n-BiPAP in twenty infants (gestational ages 24 to 31 weeks) within 6 hours of weaning from mechanical ventilation. Significant improvements in oxygen saturations and transcutaneous partial pressure of oxygen and carbon dioxide were noted during the n-BiPAP phases. There was also a significant reduction in spontaneous respiratory rate during the n-BiPAP phases. Lista et al conducted a randomised control trial of 40 babies comparing the use of n-BiPAP with n-CPAP in premature infants following Intubation-Surfactant-Extubation (InSurE) approach [7]. They showed a significant reduction in duration of respiratory support, duration of oxygen dependency and gestational age at discharge in the group receiving n-BiPAP [7].

The most commonly used method for providing n-CPAP in the UK is the Infant Flow Driver, which provides variable flow CPAP support. The Infant Flow Driver is a device which generates positive pressure at the nose by the action of a jet of gas that changes direction with variations in flow/pressure within the nose itself, reflecting the infant's respiratory activity [8]. In this way, there is variable flow, according to the phase of the infant's spontaneous respiratory effort. Prior evidence has demonstrated that n-CPAP delivered using an Infant Flow Driver is more effective both at recruiting lung volume and reducing the work of breathing in preterm infants compared with continuous flow devices [9,10]. The Infant Star ventilator delivers continuous flow n-CPAP, so the published comparisons between n-CPAP and synchronised NIPPV cited above may not be directly applicable to variable flow n-BiPAP provided using the Infant Flow Advance. The Infant Flow Advance delivers bi-level pressure by increasing the flow into the inspiratory limb of the circuit by up to 5 litres/minute (depending on the desired pressure). This increased flow enters the circuit proximal to the humidifier and there is an intrinsic time lag in delivering the increased pressure (the rise time is at best " < 1 second" - internal communication from Viasys Healthcare), which poses some doubt over whether effective synchronisation with the infant's inspiratory effort is feasible and whether the additional complication of an abdominal capsule to facilitate attempts at synchronisation is necessary.

We therefore seek to compare the use of n-BiPAP with conventional variable flow n-CPAP using the Infant Flow Advance for respiratory support post extubation in preterm infants born before 30 weeks' gestation.

### Relevance of the study to patients and service providers

The proposed study will be the first randomised trial that will aim to compare the effectiveness of n-BiPAP vs. n-CPAP in preventing extubation failure in premature babies born before 30 weeks' gestation and less than two weeks old. It will allow clinicians to have an evidence based approach to the use of n-BiPAP under these circumstances. Currently, the device is often used with shorter 'inspiratory times' which significantly compromises its performance ([name], personal communication) and without good evidence to support either its benefit or its safety.

If our hypothesis is proved correct and the use of n-BiPAP improves the chances of successful extubation, then the regular use of n-BiPAP would reduce the number of ventilator days in preterm infants. Reducing the number of ventilator days is one way of minimising chronic lung injury in premature infants. Earlier weaning and hence the reduction in number of ventilator days could have a significant positive impact on neonatal services & resources.

In the UK, facilities for the mechanical ventilation of extremely premature infants tend to be concentrated at neonatal tertiary referral centres in the National Health Service. Once infants are successfully managed off the ventilator they are transferred back to hospitals closer to home. Reduction in ventilator days would allow earlier transfer back to local hospitals with benefits to neonatal service provision and to families.

In England, 7000 preterm infants are born each year at high risk of developing chronic lung disease of prematurity/bronchopulmonary dysplasia. This condition is associated with significant morbidity and mortality. About half of affected infants continue to need supplemental oxygen at 36 weeks' gestation. The duration of ventilation during the newborn period is one of the aetiological factors involved in the development of this condition. Reduction in extubation failures and number of days on the mechanical ventilator may minimise ventilator associated lung injury and reduce this contribution to the development of chronic lung disease of prematurity. By using the Infant Flow Advance, this study is comparing two methods of delivering non-invasive support using the same widely available device in this group of infants.

## Methods

### Aims

The primary aim of this study is to compare the risk of extubation failures for 48 hours after the first extubation comparing the use of n-BiPAP or n-CPAP in infants born before 30 weeks' gestation and less than two weeks old.

### Study design

This will be an unblinded multi-centre randomised trial of n-BIPAP vs. n-CPAP in infants born before 30 weeks' gestation and less than two weeks old.

### Inclusion criteria

Infants satisfying the following inclusion criteria will be eligible to participate:

(1) Born before 30 weeks' gestation (and)

(2) Ventilated through an endotracheal tube (and)

(3) Less than two weeks old (and)

(4) Has not had first attempt at extubation (and)

(5) Parental consent has been obtained

### Exclusion criteria

Infants with the following exclusion criteria will be not be eligible to participate:

(1) Presence of major congenital malformations

(2) Presence of neuromuscular disease

(3) Presence of known upper respiratory tract abnormalities

(4) Infants requiring surgery and likely to be within 7 days post-operative at the point of extubation.

(5) Presence of intraventricular haemorrhage with parenchymal extension.

### Primary outcome measure

Failure of extubation during the first 48 hours post-extubation will be used as the primary outcome measure. 48 hours will be calculated from the hour of extubation. Failure of extubation has been defined later under 'Criteria for failure of extubation'. We have chosen 'Failure of extubation' as our primary outcome measure to maintain similarity with previous trials conducted using NIPPV. We will also measure the following secondary outcome measures.

### Secondary outcome measures

(1) Maintenance of successful extubation for 7 days from the hour of extubation

(2) Total days on ventilator, n-CPAP/n-BiPAP (anytime requiring respiratory support during a 24 hour clock will be counted as a day).

(3) Number of ventilator days following first extubation attempt (anytime requiring respiratory support during a 24 hour clock will be counted as a day).

(4) Oxygen requirement at 28 days of age and at 36 weeks' corrected gestation

(5) pH, partial pressure of carbon dioxide in the first post extubation gas

(6) Duration of hospitalisation

(7) Rates of abdominal distension requiring cessation of feeds for 7 days post extubation

(8) Rate of apnoea and bradycardia expressed as events per hour during the 48 hours following extubation

(9) Age at transfer back to referral centre in days

(10) Adverse events as described later

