### Randomisation

Infants will be randomised following the decision to extubate. Block randomisation will be used, stratified by centre and gestation (< 28 weeks or ≥ 28 weeks). Web based randomisation will be used.

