### Data collection

All data for trial analysis are routine clinical items that can be obtained from the clinical notes. Data will be collected on trial-specific case report forms. Data will be entered by the research nurse or Local principal investigator on a web based electronic case record form provided by OpenCDMS. Access to the form will be password protected and participants will be identified by trial number only.

Clinical information will be collected at the following times:

1. At trial entry: Information on eligibility; background information and randomisation

2. Following randomisation: Daily observations regarding ventilation, vital signs, blood gases, haemoglobin and C-reactive protein, apnoeas and de-saturations for 1 week after extubation

3. Follow-up: Data on duration of hospital stay, duration of oxygen requirement, oxygen requirement at 28 days and at 36 weeks corrected gestational age and age at transfer back to referral centre, total number of days on ventilator, n-CPAP and n-BiPAP

Further information will be collected on expected serious adverse events. No additional blood samples are required for this study.

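### Secondary outcome (2), total days on respiratory support, includes ventilator days that were complete before randomisation; this causes no bias but some avoidable loss of precision

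*Protocol article*

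**What the plan says.** All references are to the protocol article.

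- *Secondary outcome measures*, item (2): "Total days on ventilator, n-CPAP/n-BiPAP (anytime requiring respiratory support during a 24 hour clock will be counted as a day". No start point is given.
- Item (3) of the same list: "Number of ventilator days following first extubation attempt (anytime requiring respiratory support during a 24 hour clock will be counted as a day". This one starts at the first extubation attempt.
- Item (6): "Duration of hospitalisation", with no start point. Item (9), age at transfer back, runs from birth by construction.
- *Inclusion criteria*: the infant is on an endotracheal tube, is under two weeks old and has not yet had a first extubation attempt.
- *Randomisation*: "Infants will be randomised following the decision to extubate".
- *Data collection*: the follow-up items include "total number of days on ventilator, n-CPAP and n-BiPAP". Randomisation and background information are recorded at trial entry.
- *Statistical analysis*: secondary outcomes get ordinary, ordinal or logistic regression analogous to the primary model. That model adjusts for the stratification variables (centre and gestation band) and for further covariates still to be specified.

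**The concern.** Item (3) is expressly restricted to the time after first extubation and item (2) is not, so the word total in item (2) most naturally adds the ventilator days before extubation. Those days are over, or nearly so, when allocation is made. They are a baseline quantity inside an outcome. They carry no treatment effect, and in a linear model they add to the residual variance unless a covariate removes them.

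The section on relevance to patients and services says that, if the hypothesis is right, "then the regular use of n-BiPAP would reduce the number of ventilator days in preterm infants", and it goes on to earlier transfer and effects on services. Item (3) serves the ventilator part of that argument. Total respiratory support, invasive and non-invasive together, has no measure counted from randomisation. What is at stake is the precision of a few secondary comparisons. The primary outcome is not affected.

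**Working it through.** **The plan's own figure.** The only design calculation is for the primary outcome: 25% against 15%, two-sided 0.05, 80% power, 270 per arm. Without continuity correction, n = [1.96 × √(2 × 0.20 × 0.80) + 0.8416 × √(0.25 × 0.75 + 0.15 × 0.85)]² / 0.10² = 250 per arm. With the correction, n = (250/4) × [1 + √(1 + 4/(250 × 0.10))]² = 270. The stated figure reproduces. It says nothing about the spread of days on support.

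**Inputs for the check.**
- Upper limit of time before randomisation: under 14 days (*Inclusion criteria*).
- SD of pre-randomisation support days: not in the article. Assumed 2 to 4.04 days; 4.04 = 14/√12 is the SD if these days were spread evenly over 0 to 14.
- SD of post-randomisation support days: not in the article. Assumed 5 to 30 days.
- Correlation ρ between the two parts: not in the article. Taken as 0, then 0.3.
- 270 infants per arm (*Sample size*).

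**Formulas.** Total = pre + post, so

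Var(total) = SDpost² + SDpre² + 2ρ × SDpre × SDpost.

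Variance inflation V = Var(total) / SDpost². Set the true difference so that post-randomisation days alone give 80% power: δ = (1.96 + 0.8416) × SDpost × √(2/270). Randomisation balances the earlier days in expectation, so δ is the same for the total. Its power is then Φ(2.8016/√V − 1.96).

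Example: SDpost 5, SDpre 4.04, ρ = 0. V = 1 + 4.04²/5² = 1.653; 2.8016/1.286 − 1.96 = 0.219; Φ(0.219) = 58.7%.

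| SDpost (days) | SDpre 2, ρ = 0: V, power | SDpre 4.04, ρ = 0: V, power | SDpre 4.04, ρ = 0.3: V, power |
|---|---|---|---|
| 5 | 1.16, 73.9% | 1.65, 58.7% | 2.14, 48.3% |
| 10 | 1.04, 78.4% | 1.16, 73.8% | 1.41, 65.7% |
| 15 | 1.02, 79.3% | 1.07, 77.2% | 1.23, 71.3% |
| 20 | 1.01, 79.6% | 1.04, 78.4% | 1.16, 73.9% |
| 30 | 1.00, 79.8% | 1.02, 79.3% | 1.10, 76.2% |

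The total is the noisier measure whenever ρ > −SDpre/(2 × SDpost). At SDpre 4.04 and SDpost 10 that threshold is −4.04/20 = −0.20, so only a clear negative correlation would reverse the conclusion.

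**What adjustment does.** If the total is kept and regressed on pre-randomisation days, the residual variance is SDpost² × (1 − ρ²). At ρ = 0 this equals the variance of the post-randomisation count. At ρ = 0.3 it is 0.91 of it. In a linear model, adjusting the total therefore recovers the whole loss.

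The table applies to ordinary regression. The effect in an ordinal model was not calculated.

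**The case against.** The case for leaving the text alone has several sound parts.

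- Item (3) already supplies a ventilator count free of earlier days. A reader might infer that the aim of reducing ventilation has no clean measure; item (3) shows otherwise. The gap is confined to combined support days. Even there, the non-invasive days fall mainly after first extubation, because infants enter ventilated with no previous attempt.
- A reader might infer bias. There is none in the difference of mean days, since randomisation balances what came before it.
- A reader might take every infant as ventilated from birth, so that earlier ventilator days equal age. The article says only that infants are ventilated at entry and does not give the time of intubation.
- A reader might treat duration of hospitalisation as certainly counted from admission or birth. Its start is not stated, and an article may leave that to the full protocol.
- A reader might pick one assumed SD and report a fixed share of the 540 infants as lost. No SD in the article supports choosing one row of the table. For infants under 30 weeks, whose ventilation the *Background* says can last several weeks, the lower rows may be closer to the truth.
- The *Statistical analysis* section leaves further covariates open, so adjustment could still be specified. Gestation band is already in the model and may absorb part of any correlation.

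These points limit the size and reach of the concern. They do not remove it: item (2) is worded in the article itself, its natural reading mixes baseline with outcome, and the only covariates named are centre and gestation band.

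**Conclusion.** The point holds as a minor one. On its natural reading, outcome (2) includes up to about two weeks of ventilator days accrued before allocation, and combined support days have no version counted from randomisation. The consequence is lost precision without bias.

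With uncorrelated parts and a pre-randomisation SD of 2 to 4 days, the loss from 80% power is under 2 points when later days have an SD of 20 to 30, and about 2 to 6 points at SD 10. It reaches about 21 points only at SD 5 with the larger pre-randomisation SD. At ρ = 0.3 and pre-randomisation SD 4.04, the loss is about 4 to 6 points at SD 20 to 30 and about 14 at SD 10. All of these SDs and correlations are assumptions. For duration of hospitalisation the inclusion of earlier days is itself an inference.

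**What to change.** - **Outcome (2).** For the treatment comparison, count support days from randomisation and say how the calendar day of randomisation is handled. Alternatively, keep the total and adjust for days of support before randomisation. In a linear model both target the same difference in mean days.
- **Duration of hospitalisation and age at transfer.** State the start point of the stay, and include age at randomisation as a covariate for both outcomes. Adjustment is safer here than restarting the clock: if discharge follows postmenstrual age, a stay counted from randomisation could be noisier than the total.
- **Totals from birth to discharge** can stay as descriptive rows.

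The cost is a definition and a covariate, written into the analysis plan before treatment groups are compared. Randomisation and eligibility, which includes age, are recorded at trial entry. Total ventilator days less outcome (3) gives the ventilator days up to first extubation. Any non-invasive support before intubation would need to be identifiable from the notes. Sample size, treatment and the primary analysis do not change.

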### n-CPAP

The n-CPAP group will receive at extubation a single level continuous positive airway pressure of 6 cm water for at least 48 hours before weaning is commenced. If the infant is stable for the preceding 24 hours defined by having fewer than three minor apnoeas and no increase in oxygen requirement, weaning will be permitted. Minor apnoea will be defined as apnoea requiring stimulation but not mask ventilation. CPAP will be decreased from 6 cm water by 1 cm water every 48 hours if tolerated based on the above criteria. This will be done until a pressure of 4 cm water is reached. If a pressure of 4 cm water is successfully tolerated for 48 hours then time off n-CPAP will be allowed. Thereafter, no fixed weaning regime based on number of hours in a day the infant will be allowed to come off CPAP will be prescribed.

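### Secondary outcome 3 is named ventilator days, but its counting rule takes in any respiratory support, so days on n-CPAP or n-BiPAP score as ventilator days

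*Protocol article*

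**What the plan says.** Two secondary outcomes in the protocol article carry the same bracketed rule.

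- Item 2: "Total days on ventilator, n-CPAP/n-BiPAP (anytime requiring respiratory support during a 24 hour clock will be counted as a day".
- Item 3: "Number of ventilator days following first extubation attempt (anytime requiring respiratory support during a 24 hour clock will be counted as a day".

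Item 2 names the ventilator and both non-invasive modes. Item 3 names only the ventilator.

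The Background uses the term in the rule for the study treatments. It speaks of "less invasive forms of respiratory support such as nasal continuous positive airway pressure (n-CPAP", and it states the aim as to "compare the use of n-BiPAP with conventional variable flow n-CPAP using the Infant Flow Advance for respiratory support post extubation".

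The section on relevance to patients and service providers uses ventilator days in the narrower sense of mechanical ventilation. It expects that, if extubation succeeds more often, "the regular use of n-BiPAP would reduce the number of ventilator days in preterm infants".

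The Data collection section lists, among follow-up items, "total number of days on ventilator, n-CPAP and n-BiPAP". It gives no counting rule for item 3.

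**The concern.** The name and the rule of item 3 describe different quantities. The name is days of ventilation after the first extubation. The rule is days of any support, and after extubation that includes the randomised treatment itself.

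The article's argument for lung protection and earlier transfer to local hospitals rests on less time on the mechanical ventilator. Item 3 is the secondary outcome closest to that argument. Under the literal rule it becomes roughly the post-extubation part of item 2, and no listed secondary outcome would then isolate days of invasive ventilation.

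There is also a practical risk. Data are entered at each centre, and the two possible readings give very different counts. Centres that read the rule differently would supply figures that cannot be pooled sensibly.

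**Working it through.** **The plan's own figure.** The article gives no expected value for ventilator days. Its only design figure is 270 per arm for the primary outcome (25% vs 15%, 80% power, two-sided 0.05). It reproduces:

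- Uncorrected: n = [1.960·√(2·0.20·0.80) + 0.842·√(0.25·0.75 + 0.15·0.85)]² / 0.10² = 250 per arm.
- With continuity correction: (250/4)·[1 + √(1 + 4/(250·0.10))]² = 62.5·(2.077)² = 269.6, so 270 per arm.

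Nothing below depends on this figure or alters it.

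**Step 1: the terms.** The Background calls n-CPAP a form of respiratory support and describes both arms as respiratory support after extubation. The relevance section uses ventilator days for mechanical ventilation. No section limits the rule in item 3 to endotracheal ventilation. Taken literally, the rule therefore covers more than the outcome's name.

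**Step 2: the minimum literal score for an infant never re-intubated.** The inputs are the weaning steps in the n-CPAP and n-BiPAP sections.

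- n-CPAP: a "single level continuous positive airway pressure of 6 cm water for at least 48 hours before weaning is commenced", then 48 h at 5 cm and 48 h at 4 cm before time off is allowed. That is 3 × 48 = 144 h.
- n-BiPAP: 48 h at mean pressure 6 cm, 48 h at mean pressure 5 cm, and 48 h at CPAP 4 cm. That is 3 × 48 = 144 h.

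If support starts x hours into a clock day, it touches ⌈(x + 144)/24⌉ days:

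- x = 0: 144/24 = 6 days.
- x = 0.5, 12 or 23.5: 7 days.

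Limited to endotracheal ventilation after the first extubation, the count for the same infant is 0. The 6 to 7 days are a floor for infants who complete the sequence. Neither arm has a fixed schedule for time off support afterwards, so later part-days on CPAP would add to the count.

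**Step 3: dilution (illustration).** Take the planned failure rates, 25% and 15%. Let V be invasive days per failure and N non-invasive days per infant, with N equal in both arms and no overlap of the two on one calendar day. The article gives neither V nor N. The values below are assumptions: V from 3 to 14 and N from 6 to 30.

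- Invasive days only: the means are 0.25V and 0.15V, so the relative difference is 0.10/0.25 = 40% for any V.
- Literal rule: the means are N + 0.25V and N + 0.15V, so the relative difference is 0.10V/(N + 0.25V).

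| V | N | Mean, n-CPAP | Mean, n-BiPAP | Relative difference |
|---|---|---|---|---|
| 14 | 6 | 9.50 | 8.10 | 14.7% |
| 7 | 6 | 7.75 | 7.05 | 9.0% |
| 7 | 20 | 21.75 | 21.05 | 3.2% |
| 3 | 30 | 30.75 | 30.45 | 1.0% |

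With N equal in both arms the absolute difference, 0.10V, does not change. What is lost is its size relative to the total, and the infant-to-infant variation in non-invasive days is added as noise.

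**The case against.** The strongest reply is that nobody would apply the rule literally. Item 3 is called ventilator days. The brackets read naturally as a part-day convention copied from item 2. The Abstract lists the two outcomes separately and without the brackets. If item 3 counted all support, it would largely duplicate item 2. The Data collection section names the modes, so invasive days look derivable. The article also promises a formal statistical analysis plan, where such variables are often defined.

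Most of this stands as evidence of intent, and the intended meaning was probably invasive days. It does not remove the point, because this is not detail left for a later document. A rule is printed, and it contradicts the outcome it defines.

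A reader might infer more than the documents support:

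- **That item 3 does not measure ventilation at all.** It does. Invasive days are counted, but mixed with non-invasive ones.
- **That the rule is biased against n-BiPAP because the weaning rules differ.** The stability look-back is 24 hours for n-CPAP and 48 hours for n-BiPAP, so longer support on n-BiPAP is possible. But both sequences have the same 144-hour minimum, and nothing in the article shows a difference in duration to be likely.
- **That hours before tube removal inflate item 3.** The outcome concerns days after the first extubation. Any part-day on the day itself would arise in both arms alike.
- **That item 2 is wrong to include days before randomisation.** A total over the stay is a legitimate descriptive outcome. Randomisation balances the earlier days in expectation, so they add noise rather than bias.

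**Conclusion.** The point holds as an error of definition in one secondary outcome. Applied as written, item 3 scores at least 6 to 7 ventilator days instead of 0 for an infant who completes either weaning sequence without re-intubation. That figure rests on the literal reading and on survival through all three steps.

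The illustrated fall in the relative difference, from 40% to about 1% to 15%, also rests on assumed durations and on equal non-invasive time in the two arms. It shows the order of the dilution and is not a forecast.

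No direction of bias is established. The correction is worth making because the outcome carries the article's argument about ventilator time and the change is small.

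**What to change.** - **Item 3:** count a day only if ventilation through an endotracheal tube was given at any time in that 24-hour clock after the first extubation.
- **Item 2:** keep the rule, which fits there, and state that ventilator days and n-CPAP/n-BiPAP days are reported separately.

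The cost is the rewording of two definitions, repeated in the analysis plan and in the instructions to centres. The modes are already named under Data collection, so no new clinical information is needed. The case report form is not shown. If it holds only one combined total, the field would have to be split. Recruitment has begun, so the definition should be settled, and centres told, before the outcome is derived.
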